#### Primary outcome measures

Group comparison of suicidality measured by the score of the clinician-administered Sheehan Suicidality Tracking Scale will be conducted using analysis of covariance (ANCOVA). Baseline variables that differed significantly between groups, as well as potentially influencing risk factors, will be included in the analysis.

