### Study population and eligibility

Patients will be recruited from the four participating psychiatric hospitals in Germany (Department of Psychiatry and Psychotherapy, University Hospital Carl Gustav Carus, Dresden; Municipal Hospital Dresden, Department of Psychiatry and Psychotherapy, Dresden; Department of Psychiatry, Psychotherapy and Psychosomatics University Hospital Halle; Department of Psychiatry and Psychotherapy Furtbach Hospital, Stuttgart). All patients meeting the inclusion criteria will be informed about the study. Inclusion criteria are 18 years of age and older, admitted as an inpatient, presenting with either a mood/affective disorder (F3 section of ICD-10) or schizophrenia, schizotypal or delusional disorder (F2 section of ICD-10) and written informed consent. Patients agreeing to participate in the study have a choice to which group they want to belong to. A randomised allocation is not made for ethical reasons. Patients with legal guardians are excluded from the study. Patients are not given any incentive or compensation for participation.

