### Assessments

#### Clinician-administered scales

Sheehan Suicidality Tracking Scale (S-STS, [20]) is used to assess suicidal thoughts and/or behaviour, both clinician and self-reported. Items of the S-STS are scored on a 5-point Likert scale (0 = not at all, 1 = a little, 2 = moderately, 3 = very, and 4 = extremely). The Montgomery Asberg Depression Rating Scale (MADRS, [16]) will assess depressive symptoms; the Brief Psychiatric Rating Scale (BPRS, [17]) assesses psychotic symptoms. Investigators will also make use of the AMDP-rating scale to evaluate clinical psychopathology (Arbeitsgemeinschaft für Methodik und Dokumentation in der Psychiatrie, AMDP [19]). A rater training, as well as an evaluation of inter-rater reliability, was held at the beginning of the study to minimise differences between investigators and centres.

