### Power analysis and sample size calculation

The presented multi-centre trial is designed as a pilot study. We, therefore, did not conduct a statistical power analysis or sample size calculation. Yet, we estimate a minimum of 300 patients treated with ICD-10 F2- or F3-diagnosis in each study centre every year. Based on clinical experience, we strive for at least 100 patients per study centre.

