### Statistical analysis

Descriptive statistics covering sociodemographic and clinical baseline data will be reported using proportions, means, and standard deviations as well as Chi-square tests, *t* tests, and Mann-Whitney tests as appropriate. Results will be presented with 95% confidence intervals where applicable. Proportions of adverse events will be summarised. Sociodemographic and clinical variables that differ significantly between groups at baseline will be included as covariates in further analyses. To identify potential explanatory variables on suicidality in the weeks and months after discharge, a potential correlation of variables will be assessed by frequencies, percentages, means and standard deviations, correlation coefficients, etc. Variables that are identified as potentially influencing suicidality will be included as factors in further analyses.

Normal distribution will be assessed by Shapiro-Wilk tests and by visual inspection of histograms. Homogeneity of variances will be assessed using Levene’s test.

Statistical tests will be two-sided using an alpha level of 0.05. All analyses will be conducted using IBM SPSS Statistics for Windows, version 25.

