#### Secondary outcome measures

Group comparisons of secondary outcome measures will be conducted using analysis of (co)variance (AN(C)OVA), Poisson regression, logistic regression, *t* tests, Chi-square tests, or non-parametric methods as appropriate. The course of suicidality measured with S-STS, as well as scores of the other scales, will be analysed within groups using repeated measures AN(C)OVA for both groups separately comparing baseline values with scores at 6, 12, and 18 months.

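### Secondary group comparisons may use uncorrected Poisson models or tests without covariates, and baseline S-STS enters the primary ANCOVA only conditionally; the ANCOVA itself can stay

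*Protocol article*

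**What the plan says.** Under Primary outcome measures, the Protocol article fixes the method: "Group comparison of suicidality measured by the score of the clinician-administered Sheehan Suicidality Tracking Scale will be conducted using analysis of covariance (ANCOVA"). Covariates are the baseline variables found to differ significantly between groups, plus possible risk factors. No alternative primary test is named.

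Under Statistical analysis, "Normal distribution will be assessed by Shapiro-Wilk tests and by visual inspection of histograms", and Levene's test is used for variances. Nothing is said to follow from either result. The same section promises that baseline variables differing significantly between groups will be carried as covariates into later analyses, and adds "Statistical tests will be two-sided using an alpha level of 0.05".

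Under Secondary outcome measures, the options for group comparisons are AN(C)OVA, "Poisson regression, logistic regression", t tests, chi-square tests or non-parametric methods, to be chosen as appropriate. No option is tied to a particular variable. Methods/design says that psychiatric hospital days and psychotherapy sessions are recorded.

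Study population and eligibility lets patients choose their group, and the Discussion acknowledges that bias may result. On size, "did not conduct a statistical power analysis or sample size calculation" and "we strive for at least 100 patients per study centre".

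**The concern.** Because the groups are self-selected, covariate adjustment is the main protection for every between-group comparison. The list for secondary outcomes includes tests that in standard form take no covariates, which sits badly with the promise of covariates under Statistical analysis. The outcomes affected include the self-rated S-STS, MADRS, BPRS and VAMS.

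The one count model named assumes that the variance equals the mean. Days in hospital cluster within admissions, so that assumption is doubtful for at least one recorded variable. If it fails, the standard errors are too small and chance differences look significant.

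For the primary endpoint, the baseline value of the outcome is usually the strongest single predictor of follow-up. Making its inclusion depend on a significance test or a selection step leaves both confounding control and precision to chance.

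**Working it through.** **Inputs from the document.** "Patients will be recruited from the four participating psychiatric hospitals in Germany" and a target of at least 100 per centre give 4 × 100 = 400 recruited. The analysed number will be lower by an unstated dropout. Alpha is 0.05, two-sided. There is no power figure to reproduce.

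**Assumptions.** The split is not fixed by the plan; 200/200 is used, with 100/300 as a check. For the score, "Items of the S-STS are scored on a 5-point Likert scale (0 = not at all"; no share of zeros, SD, dispersion or baseline correlation is given, so all of these are assumed.

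**1. Is the primary ANCOVA valid?** Simulation, 2,000 runs per scenario, 50% or 70% zeros, baseline correlation 0.5 on the latent scale: type I error 0.045 to 0.050 at 200/200, 100/300, 140/140 and 70/210. Shapiro-Wilk on the residuals rejected in essentially every run, so the test carries no information here.

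Power at 200/200:

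| Assumed effect | Raw ANCOVA | Log ANCOVA | Rank ANCOVA | Unadjusted Mann-Whitney |
|---|---|---|---|---|
| Zeros 50% to 60% only | 0.30 | 0.50 | 0.55 | 0.47 |
| Zeros and severity | 0.87 | 0.83 | 0.78 | 0.69 |
| Severity only, 50% zeros | 0.87 | 0.44 | 0.24 | 0.20 |
| Severity only, 70% zeros | 0.57 | 0.22 | 0.08 | 0.08 |

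A separate run of 400 per scenario (Monte Carlo error about 2.5 points) set raw ANCOVA against robust negative binomial: 0.30 v 0.30 (zeros only), 0.80 v 0.76 (both), 0.90 v 0.81 and 0.59 v 0.48 (severity only, 50% and 70% zeros). Further runs on similar data gave 0.32 v 0.31, 0.77 v 0.74 and 0.82 v 0.85.

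**2. Poisson without correction.** If the true variance is φ times the mean, the nominal 5% test rejects a true null with probability 2Φ(−1.96/√φ).

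| φ | Type I error |
|---|---|
| 1 | 0.05 |
| 1.5 | 0.11 |
| 2 | 0.17 |
| 5 | 0.38 |
| 10 | 0.54 |
| 40 | 0.76 |

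Simulated hospital days (40% readmitted, mean 31 days, φ about 39) gave 0.76, and 0.048 after a scale correction. Another simulation gave 0.74, and 0.03 with robust errors. Rare counts such as attempts (mean 0.1, φ about 1.2) gave only 0.07.

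**3. Unadjusted tests in self-selected groups.** Let the groups differ at baseline by δ SD, let baseline and follow-up correlate at ρ, and let there be no group effect given baseline. The unadjusted follow-up difference is then ρδ SD. Its standard error is √(2/200) = 0.1 SD, so λ = ρδ/0.1 and the rejection rate is Φ(λ − 1.96) + Φ(−λ − 1.96). For δ = 0.3:

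- ρ = 0.3: λ = 0.9, rate 0.15
- ρ = 0.4: λ = 1.2, rate 0.22
- ρ = 0.5: λ = 1.5, rate 0.32

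Simulations on skewed scores agree in order of size. At δ = 0.3, one gave 11% for Mann-Whitney and another 24 to 29% for rank and t tests. At δ = 0.5 and 0.8, Mann-Whitney gave 23% and 55%. Baseline-adjusted models stayed at 5 to 6%.

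**4. Conditional inclusion of baseline S-STS.** A baseline t test detects an imbalance δ with probability Φ(δ/0.1 − 1.96) + Φ(−δ/0.1 − 1.96). For δ = 0.2 this is Φ(0.04) + Φ(−3.96) = 0.52, so such an imbalance is missed about half the time. Left out at ρ = 0.5, it carries 0.5 × 0.2 = 0.1 SD of bias. Precision is lost as well. The standardised difference detectable with 80% power is (1.96 + 0.84) × 0.1 = 0.28 without baseline, and 0.28 × √(1 − 0.25) = 0.24 with it.

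**The case against.** The best defence is that this is a condensed article on a pilot study. The model for each variable and the handling of dispersion commonly belong in the full protocol or SAP. Poisson is one option in a list and hospital days are not assigned to it; covariates are the stated default under Statistical analysis; and baseline S-STS would probably be picked up as a risk factor. Much of this stands. The type I error figures are conditional on a choice the plan permits but does not make, and on assumed distributions. They are not predictions of what the trial will do. What remains is that the article itself names these methods, and that the covariate promise and the list of tests without covariates pull in different directions.

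Three stronger readings are tempting and not supported:

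- **Raw-score ANCOVA wastes power and should be replaced.** A simulation with a pure log-mean shift gave 0.51 against 0.71 for negative binomial, but that effect is built on the negative binomial's own scale. Under the other effects tried, ANCOVA did about as well or better than negative binomial. Log and rank ANCOVA overtook it only when the effect lay in the share of zeros alone.
- **Shapiro-Wilk will push the primary analysis to a rank test.** The plan attaches no switch to it, also uses histograms, and names non-parametric options for outcome comparisons only among the secondary outcomes.
- **Hospital days will be analysed by plain Poisson.** The document does not say so.

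**Conclusion.** The primary ANCOVA is valid at the planned size and need not be changed; a log-link or ordinal model is at most a sensitivity analysis. Three smaller points hold.

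- The only named count model is anticonservative if counts are overdispersed: type I error 0.17 at φ = 2 and about 0.75 near φ = 40. This matters for day counts and little for rare events.
- The unadjusted options for secondary outcomes forgo confounding control in self-selected groups: 11 to 29% false rejection in simulation at an assumed 0.3 SD imbalance, against 5 to 6% adjusted.
- Baseline S-STS is not guaranteed a place in the primary model.

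The sizes rest on an assumed 200/200 split, assumed score and count distributions, and an assumed baseline correlation. The direction of each point depends only on overdispersion, baseline imbalance and correlation being present to some degree. These are modest but worthwhile corrections.

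**What to change.** Four changes of wording, using data already collected:

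1. For counts such as hospital days and psychotherapy sessions, replace plain Poisson by negative binomial, or by Poisson with robust or scale-corrected standard errors, with log follow-up time as offset.
2. State that every between-group comparison of an outcome uses a covariate-adjusted model, and that Shapiro-Wilk and Levene results do not trigger a change to an unadjusted test.
3. Include baseline clinician-rated S-STS in the primary ANCOVA whether or not it differs significantly between groups.
4. Optionally, add an adjusted log-link or ordinal model of S-STS as a sensitivity analysis.

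The cost is small: count effects are reported as rate ratios, and their intervals will be somewhat wider than plain Poisson would give.

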#### Secondary outcome measures

Group comparisons of secondary outcome measures will be conducted using analysis of (co)variance (AN(C)OVA), Poisson regression, logistic regression, *t* tests, Chi-square tests, or non-parametric methods as appropriate. The course of suicidality measured with S-STS, as well as scores of the other scales, will be analysed within groups using repeated measures AN(C)OVA for both groups separately comparing baseline values with scores at 6, 12, and 18 months.

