**Fig. 1 Fig1:**
[figure not shown]
Trial flow

Both groups will receive treatment as usual in terms of regular meetings with their general practitioner, psychiatrist, and/or psychotherapist. The idea of the present study is to create a four eyes principle. The study setting includes an option to connect with the patients’ doctors or therapists as well as a person the patient chose in advance. It applies in case of health-related severe events (e.g., increasing suicide risk, suicide attempt). It enables the investigator to provide support, e.g., by coordinating further procedures with the patients’ psychiatrist/psychotherapist (provided that the patient voted for this option in written consent). If confronted with acute suicide risk, the investigator may also decide to follow the hospital’s emergency procedure in case of risk of self-harm and immediately present the participant to a psychiatrist on site. Connecting with doctors and therapists or a close person will also be possible in case of non-appearance to an appointment combined with a failure to reach the patient. This also allows us to gain important information on a potential suicide risk or suicide*.*

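### The repeated measures AN(C)OVA planned for the course of suicidality keeps only patients with scores at all four visits; a mixed model in the same software would use every score collected

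*Protocol article*

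**What the plan says.** Under Secondary outcome measures, the protocol article fixes the method for "The course of suicidality measured with S-STS, as well as scores of the other scales": these "will be analysed within groups using repeated measures AN(C)OVA for both groups separately comparing baseline values with scores at 6, 12, and 18 months". The analysis therefore has four levels (baseline, V6, V12, V18) and is run once in each group.

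Under Statistical analysis, the software is fixed: "All analyses will be conducted using IBM SPSS Statistics for Windows, version 25". Neither place mentions imputation, a mixed model or any other way of keeping patients with incomplete scores in this analysis.

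The document does foresee missed visits. The text after Fig. 1 in the Course section plans for patients who do not attend and cannot be reached: "Connecting with doctors and therapists or a close person will also be possible in case of non-appearance to an appointment". It also contains measures that limit the problem. Telephone visits are accepted as alternatives (Methods/design), the schedule continues through readmission (Methods/design and Course), and visits have windows of 1 to 2 weeks (Course).

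The primary between-group comparison is a separate analysis, an ANCOVA (Primary outcome measures).

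**The concern.** Repeated measures AN(C)OVA, as the SPSS repeated measures GLM procedure runs it, treats the four scores as one record and removes the whole record if any score is missing. A patient seen at V6 and V12 who withdraws before V18 contributes nothing. Neither does a patient who attends V18 but missed V6. The analysed set is thus patients with all four scores, which is narrower than patients still present at 18 months.

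Two things are at stake. The first is information, because scores already collected are discarded. The second is who is described. One of the study's two stated aims is to understand suicidality after discharge, and the document itself treats an unreachable patient as a possible sign of suicide risk. If attendance is related to suicidality, the patients with four scores are not a random subset of those enrolled.

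**Working it through.** The article gives no power calculation, dropout rate or attendance rate, so there is no figure of its own to reproduce. Every rate below is an assumption.

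**Target sample.** The protocol states "we strive for at least 100 patients per study centre", and "Patients will be recruited from the four participating psychiatric hospitals in Germany". Target N = 4 × 100 = 400 over both groups. The split is unknown because patients choose their group.

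**Step 1: patients retained.** Baseline is taken as complete. If each of the three follow-up visits is missed independently with probability m, the number with all four scores is N × (1 − m)³. The number with at least one follow-up score is N × (1 − m³). Follow-up scores collected are 3 × N × (1 − m).

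| m | All four scores | At least one follow-up score | Follow-up scores collected | Used by repeated measures AN(C)OVA |
|---|---|---|---|---|
| 10% | 400 × 0.729 = 292 | 400 × 0.999 = 400 | 1,080 | 3 × 291.6 = 875 |
| 20% | 400 × 0.512 = 205 | 400 × 0.992 = 397 | 960 | 3 × 204.8 = 614 |
| 30% | 400 × 0.343 = 137 | 400 × 0.973 = 389 | 840 | 3 × 137.2 = 412 |

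Independent misses give a heavy loss. If instead the same patients drop out for good, the loss equals the dropout by month 18: dropout of 10%, 20%, 30%, 40% or 50% leaves 360, 320, 280, 240 or 200 patients.

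**Step 2: bias if withdrawal follows high scores.** Simulation in large samples with a true mean of 0 at all four visits, SD 1 and correlation 0.6 between visits. Withdrawal before each follow-up visit is logistic in the previous score, with intercept −1.7 and slope 1.0. The odds of withdrawal thus rise by a factor of e^1.0 = 2.7 per SD. Withdrawal averages about 18% per 6 months, and 0.82³ = 55% complete.

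| | V0 | V6 | V12 | V18 |
|---|---|---|---|---|
| Mean in patients with all four scores (truth 0) | −0.32 | −0.32 | −0.32 | −0.26 |
| Change from V0 (truth 0) | – | 0.00 | 0.00 | +0.06 |
| Likelihood estimate from all available scores | 0.00 | 0.00 | 0.00 | 0.00 |

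The levels are too low throughout. The contrasts with baseline, which are what the protocol tests, are almost correct, because the retained patients also start low. The one error in change points upward.

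A milder scenario (correlation 0.5, odds doubled per SD) gives the same pattern. With 20% dropout by month 18, the means are low by 0.07 to 0.09 SD; with 40%, by 0.15 to 0.20 SD.

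**Step 3: the primary ANCOVA at V18.** With equal dependence of withdrawal on score in both groups, the spurious group difference is 0.002 SD. With slope 1.0 in one group and 0.3 in the other, it is about 0.05 SD. For 200 patients per group (an even split, assumed) and this dropout, the standard error is about 0.10 SD, so that bias is about half a standard error.

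**The case against.** **The article is condensed and an unseen analysis plan may impute first.** This is fair as far as it goes. Repeated measures AN(C)OVA after imputation deletes nobody, and the term is sometimes used loosely for a mixed model. The deletion is therefore conditional on the classical form. But the article names a specific method and software and nothing that offsets the deletion, so a plan that follows this text inherits it. The point is about a stated choice and does not allege an omission.

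**Missed visits may be few.** Telephone visits, visit windows and continuation during readmission should all keep losses down, and deterioration leading to readmission does not by itself end participation. This stands: the 20% and 30% rows may be pessimistic. These measures reduce missing data but do not change how the analysis treats what is still missing.

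**A reader might infer that suicidality at 12 and 18 months would be understated relative to baseline.** The calculation does not support this. Baseline is understated by about as much, so the change is nearly unbiased in this scenario. A larger error in change would need further assumptions, such as different trajectories in those who leave.

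**A reader might also infer that the primary analysis has the same defect.** It does not. That analysis "will be conducted using analysis of covariance (ANCOVA"), not repeated measures, so this deletion rule does not apply. An ANCOVA at V12 or V18 does leave earlier follow-up scores of withdrawn patients unused. The resulting bias is about 0.05 SD, and only if withdrawal depends on score differently in the two groups. Self-chosen group membership limits that comparison more.

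**It is a secondary, within-group analysis in a declared pilot.** True, and this limits the weight of the point. It does not justify discarding data already in hand.

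**Conclusion.** The point holds for the secondary within-group course analysis. As written, and in its classical form, the method restricts the analysis to patients with all four scores. The loss would be 108, 195 or 263 of 400 patients (400 minus 292, 205 or 137) at assumed independent miss rates of 10%, 20% or 30%. If withdrawal follows high scores as assumed, the reported levels are about 0.26 to 0.32 SD too low at every visit, and the change from baseline is off by at most about 0.06 SD.

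The deletion follows from the method. Its size depends on attendance rates that the document does not give, and the direction of the bias in levels depends on worse patients leaving more often, which is plausible but assumed. The main costs are lost precision and a selected sample. This is a worthwhile and cheap improvement; it does not show that the planned result would be materially wrong.

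**What to change.** Under Secondary outcome measures, replace the repeated measures AN(C)OVA with a linear mixed model for repeated measures fitted to all available scores. Baseline should be one of the four outcome occasions, with visit as a factor and an unstructured covariance. The contrasts of baseline with 6, 12 and 18 months stay as they are. Report the number of patients scored at each visit by group, so that readers can see who is described.

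The cost is one sentence. The model runs as MIXED in the SPSS version already named and needs no further patients, visits or data. The downside is a slightly more complex model. It corrects for withdrawal that depends on scores already observed, but not for withdrawal driven by deterioration that was never recorded.

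Taking the V12 and V18 primary comparisons from the same type of model is optional, given the small bias there.

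### The covariate rule for baseline imbalance is not kept out of the within-group course test, where it corrects nothing and can distort the test of time

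*Protocol article*

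**What the plan says.** Three statements in the protocol article combine.

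- *Statistical analysis* sets a general rule: "Sociodemographic and clinical variables that differ significantly between groups at baseline will be included as covariates in further analyses". It names no analysis to which the rule does not apply. A companion rule reads: "Variables that are identified as potentially influencing suicidality will be included as factors in further analyses".
- *Secondary outcome measures* defines the course analysis of the S-STS and the other scales: "repeated measures AN(C)OVA for both groups separately comparing baseline values with scores at 6, 12, and 18 months". Baseline is therefore one of the four levels of the outcome, and the bracketed C admits covariates.
- *Statistical analysis* also fixes the test level ("Statistical tests will be two-sided using an alpha level of 0.05") and the software ("All analyses will be conducted using IBM SPSS Statistics for Windows, version 25"). It does not mention centring of covariates.

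Under *Study population and eligibility*, groups are formed by preference: "Patients agreeing to participate in the study have a choice to which group they want to belong to". The Discussion acknowledges that this may cause bias. Significant baseline differences, and so use of the covariate rule, are a realistic prospect.

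**The concern.** The rule has a purpose when two self-selected groups are compared. It has none inside one group: each patient is compared with himself or herself, and a difference from the other group cannot confound that comparison.

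The covariate may also do harm. In a repeated measures ANCOVA, the main effect of time is the intercept of the change scores regressed on the covariate. With an uncentred continuous covariate, that intercept is the expected change in a patient whose covariate is zero, for instance aged zero. The extreme case is the scale's own baseline score. It is a clinical baseline variable, and nothing bars it from being both the first outcome level and the covariate.

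The p-value for the course would then not belong to the mean change reported beside it. Because the rule selects variables whose means differ between groups, the distortion would also differ between groups. One group could show a significant course and the other none for no clinical reason.

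**Working it through.** The article states no power or error-rate figure beyond alpha 0.05, so there is none to reproduce (it "did not conduct a statistical power analysis or sample size calculation").

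**Inputs from the article.** Four outcome levels (baseline, 6, 12 and 18 months); two-sided alpha 0.05; on size, "we strive for at least 100 patients per study centre" in four centres, so 4 × 100 = 400 patients, or 200 per group if evenly split. The split and the dropout are not given.

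**Assumed inputs.** 50–200 patients per group, normal scores, and the means, SDs and correlations shown below.

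**What is tested when no mean changes.** Let x be an uncentred covariate correlated r_b with the baseline score and r_f with each follow-up score. The tested change from baseline is

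(r_b − r_f) × SD_y × mean_x / SD_x.

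If x is the scale's own baseline, r_b = 1 and this becomes (1 − r) × baseline mean, with r the between-visit correlation. Both are non-zero although nothing changed, unless r_b = r_f.

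**Own baseline as covariate, no true change** (multivariate test of time, 2000 runs per row):

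| Mean, SD, r | Tested value | n | Uncentred | Centred | No covariate |
|---|---|---|---|---|---|
| 8, 7, 0.4 | 0.6 × 8 = 4.8 | 100 | 100% | 10–11% | 5% |
| 4, 5, 0.5 | 0.5 × 4 = 2.0 | 150 | about 100% | 9–10% | 5% |
| 2, 4, 0.6 | 0.4 × 2 = 0.8 | 150 | 84–87% | 7–8% | 5% |
| 2, 4, 0.6 | 0.4 × 2 = 0.8 | 100 | 64–67% | 7–8% | 5% |

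Ranges reflect repeated simulations. Over all own-baseline settings, the centred version rejects in 7–12%.

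**Other covariates, uncentred, no true change** (n = 50 / 100 / 200 per group):

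| Covariate (mean, SD) | r_b, r_f | Tested value in SD_y | Rejection |
|---|---|---|---|
| Symptom score (15, 8) | 0.6, 0.3 | 0.3 × 15/8 = 0.56 | 49 / 81 / 98% |
| Symptom score (15, 8) | 0.5, 0.4 | 0.1 × 15/8 = 0.19 | 8 / 13 / 21% |
| Age (45, 15) | 0.3, 0 | 0.3 × 3 = 0.90 | 54 / 86 / 99% |
| Age (45, 15) | 0.2, 0.1 | 0.1 × 3 = 0.30 | 9 / 15 / 25% |
| Age (45, 15) | 0.2, 0.2 | 0 | 5 / 5 / 4% |

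Centred, these cases reject in 4–7%; without the covariate, in 4–6%.

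**Power.** With equal correlations the type I error holds, but the standard error of the time effect grows by √(1 + (mean_x/SD_x)²). For age 45, SD 15, that is √(1 + 9) = 3.16. For a true fall of 0.3 SD, power drops from 53 / 89 / 99% without the covariate to 9 / 15 / 26% with it uncentred (n = 50 / 100 / 200). For a 2-point fall at n = 150 with age 45, SD 14 (factor √(1 + (45/14)²) = 3.37), it drops from 92% to 13–15%.

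**A real fall with own baseline as covariate** (baseline mean 8, SD 7, r = 0.4, n = 150). The tested value is the follow-up mean minus 0.4 × 8 = 3.2. Rejection is 72% for a fall to 5.0, 43% to 4.5, 18% to 4.0, 5% to 3.2 and 37–40% to 2.0. Without the covariate each of these falls is detected in essentially 100%. The 5% is the minimum, because at 3.2 the tested value is exactly zero.

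**The case against.** **Scope of the rule.** *Secondary outcome measures* does not say that imbalanced variables enter the course test; the bracketed C leaves covariates optional. *Primary outcome measures* repeats the imbalance rule for the group comparison, while the paragraph on course does not. A reader may confine the rule to between-group comparisons. That reading is open, but so is the other: the rule is worded without exception and the course test explicitly allows covariates.

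**Coding.** Uncentred entry is nowhere stated. Only the software is named, and how it handles covariates is not in the article. This stands, and the large error rates are conditional on it. Centring does not settle everything: with own baseline as covariate 7–12% remains, and a covariate still has no confounding to remove.

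**Worst case.** A reader might infer that the planned course test will almost always be significant when nothing has changed. The article does not support that. It does not prescribe own baseline as a covariate, gives no data showing that S-STS or MADRS will differ between groups, and supplies none of the means or correlations. A covariate equally correlated with all visits causes no type I inflation, and variables entered as categorical factors do not cause the problem.

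**Use of covariates.** A covariate-by-time term can show whose scores change, which serves the aim of identifying factors in suicide risk. This stands, but as a separate question from whether the group mean changed.

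**Consequence.** The analysis is secondary and within-group, in a pilot, and the reported means and confidence intervals would reveal a flat mean beside a discordant p-value. This limits the weight of the point but does not remove it.

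**Conclusion.** The point holds in conditional form. Followed as written, the plan can put baseline-imbalanced covariates, even a scale's own baseline, into a one-group test of time where the imbalance cannot confound.

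If the covariate is continuous and uncentred, the test no longer addresses the mean change. With own baseline as covariate and flat means, rejection is about 64–100% at 100–150 patients per group instead of 5%, and 7–12% if centred. Other covariates range from no inflation with severe power loss to strong inflation when correlations with baseline and follow-up differ. All sizes rest on assumed means, SDs and correlations and on simulated normal scores.

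The primary between-group ANCOVA is not affected by this mechanism, and nothing here bears on its validity. The text should be corrected because the rule is misapplied to this test and the remedy is simple; it is not a threat to the study's main comparison.

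**What to change.** In *Statistical analysis*, state that the rule on baseline-imbalanced covariates applies to between-group comparisons only. In *Secondary outcome measures*, test the within-group effect of time without covariates, so that AN(C)OVA becomes ANOVA for that analysis.

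If a covariate-by-time term is wanted to explore who changes, centre the covariate at its mean, do not use the scale's own baseline while baseline is a level of time, and still take the time effect from the covariate-free model.

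The cost is a sentence in the analysis section; no extra data or patients are needed. The small downside is that the time test is no longer covariate-adjusted, and covariate-by-time results become a separate exploratory analysis.
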